#### 30-Second Chair Stand Test

This will be conducted by having the patient perform as many sit–stand–sit cycles as possible during a 30-s test (Macfarlane et al., 2006; Millor et al., 2013), with the number of cycles completed recorded. This test will be conducted at the Salvation Army Treatment Center.

#### 1-Minute Burpee Test

This is a functional test and outcome measure. The burpee is a total body exercise used in strength training, high-intensity training, and aerobic exercise. It is designed to develop strength, agility, coordination, and aerobic performance. The test starts with the subjects in a standing position with their feet shoulder-width apart. They then drop into a squat position with their feet underneath them and their hands on the ground and quickly extend their feet in one motion to assume the front plank position with legs completely extended and back straight. Finally, they return to the squat position and then jump straight into the air as high as possible. Repeat. This entire exercise is intended to be performed in a fluid, rapid movement (Gist et al., 2014).

### Physical Exercise/Intervention Protocol

The study uses HIIT/HICT consisting of functional exercise movements combined with primitive reflex training exercises conducted in a 4-week program to examine the effects of this protocol on the recovery of cognitive function after chronic SUD. In the current literature, high-intensity training is considered a high-yield training form and usually includes three types of exercise (Unhjem et al., 2016). The best evidence indicates that a minimum of three 30–60-min sessions are needed per week (Milanović et al., 2015; Eddolls et al., 2017), over the course of 4–9 weeks of training. Because our patient population has relatively short-term stays in the facility, we set the control and intervention periods as 4 weeks each. As noted, the physical exercise protocol for the intervention group consists of four 30-min sessions per week, with an active warm-up included in each session. Each of the 30-min exercise sessions will be the same, with a target heart rate of 70–90% of the patient’s maximum heart rate (220 beats per minute minus the patient’s age). Each training session consists of a warm-up period at 60–70% of maximum heart rate (114–133 bpm), followed by exercise performed at 70–90% of maximum heart rate (134–170 bpm), with a cutoff at 90% (171 bpm), and then an active cooldown period. Polar heart rate zones will be used to control the exercise intensity throughout the training sessions. Because of the low cost and limited need for equipment, we plan to use body weight functional exercises in this study. The exercises for each training session will be performed at nine stations, with 45 s of work at each station and 15 s to rest and change stations. Participants will complete three circuits of the nine stations, with 25 s of rest between circuits. The active cooldown consists of walking for 5 min. The nine exercises are: air squats; cat/camel; reverse rowing with a sling; starfish; burpees; frog sit-ups/CrossFit sit-ups; crawling [asymmetrical tonic neck reflex (ATNR) exercise]; jumping jacks; and push-ups. Supplementary Appendix A contains further description and information about the exercises in the protocol.

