## Abstract

This proposed study will examine whether structured physical activity reduces the recovery time of cognitive functioning during the early phase of substance use disorder treatment. Addiction or substance dependence is associated with neurobiological changes and cognitive impairment that can affect quality of life and the efficacy of therapy for up to a year after clinical detoxification. The biological, psychological, and social effects of physical exercise have the potential to be a therapeutic approach to increase quality of life and relieve symptoms associated with substance abuse, such as psychosis, depression, and anxiety. There is a dearth of research on physical activity and exercise in clinical substance use disorder patients. This protocol describes a clinical study that will examine cognitive recovery after substance abuse using physical exercise as a treatment intervention. We will use a quasi-experimental longitudinal clinical trial, with a pretest and multiple posttests, on naturally randomized sequential groups. Patients will be consecutively be recruited into the study groups, with a control group that is completed, before its followed by an intervention group, each with 30 patients. Patients will be enrolled 2 weeks after the start of detoxification, at which time all subjects will be inpatients at the Stavanger Salvation Army Treatment Center in the Norwegian specialized healthcare system. Cognition will be evaluated with a comprehensive battery of cognitive tests, including several tests of executive function. Physical fitness will be tested with the Rockport 1-Mile Walk Test, the 30-S Chair Stand Test, the 1-Min Burpee Test at baseline (within the first 2 weeks of admittance) and after 4 weeks. The intervention will be a 30-min workout at 70–90% of maximum heart rate (134–170 bpm), recorded and calculated by a Polar heart rate monitor. The intervention treatment will be administered four times a week for 4 weeks and will consist of high-intensity circuit training, high-intensity interval training, functional movement, and primitive reflex training. We anticipate improvement in both the control and intervention groups, with the exercise intervention group having the greatest increase in recovery of cognitive function because of the combination of functional full body movements and primitive movement training in an intense interval training program.

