1.This study protocol is designed to investigate the impacts of HIIT and HICT combined with functional exercises and primitive reflex training on quality of life and cognitive functioning for patients with SUD. Specifically, the protocol will examine whether structured physical activity improves cognitive functioning for SUD patients relative to that of SUD patients in a control group.2.We will examine whether different intensities of physical activity, such as HIIT/HICT versus other types of physical activity (e.g., hiking) are associated with different cognitive recovery trajectories during the subacute phase of SUD treatment.

This research protocol has several possible applications. First, it will enable future studies to reproduce the exercise protocol and increase the knowledge base on SUD and the effects of exercise. One of the more significant problems in the exercise literature is the inadequate description of exercise, such as the dose, intensity, and how exercises are implemented in studies, which limits reproducibility. This protocol and training regime would serve as a base for comparisons with other workout routines, types of exercises, and duration of exercises. Because this exercise regime will be compared with control group activities, it will be validated as having positive or negative effects for SUD patients in a subacute clinical setting.

Second, because there are so few studies on exercise and substance abuse, a protocol will make it easier to reproduce and increase the number of studies with identical exercise regimes by using this protocol as a guide. This would facilitate comparisons between studies and allow for systematic reviews and meta-analyses.

Third, if this protocol leads to an effective intervention which improves the participants’ cognitive functioning and quality of life, the training regime would be inexpensive and easy to implement in a clinical setting, as there is no need for specialized equipment or extensive staff training.

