## Stepwise Procedures

Recruitment and eligibility. Patients will be recruited from the Helse Vest catchment area via the subacute treatment facility FAB. The Helse Vest catchment area consist of western Norway. FAB is mainly recruiting form the county of Rogaland and the main cities in the region Stavanger, Sandnes, and Haugesund. The patient target group for FAB is refered patients from the specialized health care system, with an addiction so serious that inpatient treatment is deemed necessary by a evaluation center. Comorbidity of light psychiatric diagnoses are accepted. We included patients of 18 years of age and upward. The patients often receive social benefits or disability pension. Education among the patient group is mixed from elementary school to university educated. We included patients mixed between first time rehabilitation to varying number of previous admission. Eligibility: SUD diagnosis, admitted as an inpatient to FAB; ≥18 years of age; passes the physical evaluation for the institution to perform intensive training; no medical history or illness that precludes participation in physical activity; and psychiatric diagnoses no more serious than the grading of light to moderate. Patients will be excluded from the study if their medical history (e.g., physical disability, disease, or injury) could interfere with or be exacerbated by physical activity. For example, patients with paralysis, severe pain, obstructive disease, glaucoma, or who are unable to sit, stand, and/or walk will be excluded, as well as patients with a severe cognitive deficit, such as dementia. A severe cognitive deficiency will be assessed based on the patients’ responses to two questions: “Do you have trouble with your memory that affects your daily life?” and “Have you been given a medical diagnosed of dementia?” Protocol deviations: If participants are absent from more than 60% of the training sessions. They are considered protocol violators. If they are not able to participate at allocated test times and complete the tests, they are considered protocol violators. They are still included in the study and tested as soon as possible. Statistical analyses will be performed both based on the principle of “intention to treat” including everyone regardless of protocol violation and “per protocol” analyses will be performed, comparing only those that have completed the protocol.

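### The printed heart-rate limits (114–133, 134–170, cutoff 171 bpm) fit only a 30-year-old, although intensity is defined by each patient's own 220 minus age

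*Protocol article*

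**What the plan says.** The Physical Exercise/Intervention Protocol section sets the target at "70–90% of the patient’s maximum heart rate (220 beats per minute minus the patient’s age"), which is a rule specific to each patient. The next sentence turns the percentages into fixed values. Warm-up at 60–70% is printed as 114–133 bpm, "followed by exercise performed at 70–90% of maximum heart rate (134–170 bpm), with a cutoff at 90% (171 bpm"). The Abstract describes the intervention as a "30-min workout at 70–90% of maximum heart rate (134–170 bpm), recorded and calculated by a Polar heart rate monitor", with no mention of age.

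On control of intensity, the same section says that "Polar heart rate zones will be used to control the exercise intensity throughout the training sessions". It does not say how those zones are set. On age, Stepwise Procedures says "We included patients of 18 years of age and upward" and states no upper limit.

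On session length, the section describes "four 30-min sessions per week, with an active warm-up included in each session". It gives nine stations of 45 s work and 15 s change, and says "Participants will complete three circuits of the nine stations, with 25 s of rest between circuits". It then adds a 5-minute walking cooldown.

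**The concern.** The percentage rule yields a different bpm range at each age, yet only one range is printed and nothing marks it as an example. The two statements cannot both hold for a group of adults of mixed age.

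Intensity is the defining feature of this intervention, and the second aim in the Introduction concerns different intensities of activity. The 171 bpm figure is also the only numerical upper limit in the text, so it serves as a safety threshold. If it were applied as printed, older patients could train above the intended 90% limit, while the youngest could fall short of the intended dose and still count as on target.

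The Introduction criticises other work for "inadequate description of exercise, such as the dose, intensity, and how exercises are implemented in studies, which limits reproducibility" and offers this protocol for others to reproduce. A bpm number is the easiest item to copy into a monitor or into another protocol.

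**Working it through.** **Inputs.** Maximum = 220 − age; warm-up 60–70%, work 70–90%, cutoff 90%; printed limits 114, 133, 134, 170 and 171 bpm (all from Physical Exercise/Intervention Protocol). Eligible age is 18 and over (Stepwise Procedures). The document gives no age distribution, so the ages below are an assumed range.

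**Reproducing the printed figures.** With a maximum of 190 bpm:
- 0.60 × 190 = 114
- 0.70 × 190 = 133
- 0.90 × 190 = 171

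The values 134 and 170 are the adjacent whole beats that keep the zones from overlapping. Since 190 = 220 − 30, the age is 30. Over ages 18 to 89, with rounding to the nearest beat, only age 30 gives 114, 133 and 171. Rounding down also admits 29, and rounding up also admits 31.

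**Applying the rule at other ages.** Correct limit = fraction × (220 − age); printed limit as a share of maximum = bpm ÷ (220 − age).

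| Age | Maximum | Correct 60% | Correct 70% | Correct 90% | 134 bpm as % of max | 171 bpm as % of max | 171 minus correct 90% |
|---|---|---|---|---|---|---|---|
| 18 | 202 | 121.2 | 141.4 | 181.8 | 66.3 | 84.7 | −10.8 |
| 20 | 200 | 120 | 140 | 180 | 67.0 | 85.5 | −9 |
| 30 | 190 | 114 | 133 | 171 | 70.5 | 90.0 | 0 |
| 40 | 180 | 108 | 126 | 162 | 74.4 | 95.0 | +9 |
| 50 | 170 | 102 | 119 | 153 | 78.8 | 100.6 | +18 |
| 60 | 160 | 96 | 112 | 144 | 83.8 | 106.9 | +27 |

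**Where the limits cross.**
- Cutoff: 171/190 = 90.0% at 30 and 171/189 = 90.5% at 31, so it is too high from 31 on. At 49, 171/171 = 100.0%, so from there it equals or exceeds the predicted maximum.
- Floor: 134/192 = 69.8% at 28 and 134/191 = 70.2% at 29, so it is too low from 18 to 28. At 28 the shortfall is only 0.7 × 192 − 134 = 0.4 bpm; at 18 it is 141.4 − 134 = 7.4 bpm.
- Warm-up: at 60, the printed 114–133 bpm is 71.2–83.1% of maximum, which lies inside the work zone.

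**Session length (secondary).** Three circuits × nine stations × 60 s + two rests × 25 s = 1,620 + 50 = 1,670 s = 27:50. Adding the 5:00 cooldown gives 32:50 before any warm-up. Dropping the last 15-s change in each circuit gives 27:05 and 32:05. If the cooldown lies outside the 30 minutes, 2:10 (or 2:55) is left for warm-up. The work dose is fixed either way: 27 × 45 s = 20:15 per session, and × 16 sessions = 324 min.

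**The case against.** The strongest reply is that the individual rule comes first and plainly governs. Each bpm figure stands in parentheses beside a percentage, so a trainer following the text has what is needed at any age. The Abstract has the monitor calculating as well as recording, which suggests zones derived from each patient's age. No sum is wrong at 190 bpm; what is missing is a label. Patients must also pass a physical evaluation for intensive training.

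Most of this stands, and it makes the harm conditional. It does not remove the conflict. Neither section says that zones are set per patient, and the Abstract's clause about the monitor itself carries the fixed 134–170 bpm range. The physical evaluation screens patients but does not correct the limits.

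Two refinements are fair. The floor error at 28 is under half a beat. Also, 220 minus age is a prediction, so the proper statement about age 49 and over is that 171 bpm equals or exceeds the predicted maximum, not that no patient could reach it.

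On session length, 30 minutes may be nominal with the cooldown outside it, and a condensed article may omit the warm-up length. The section does, however, list the cooldown as part of the session.

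**Conclusion.** Wrong as written. The printed limits agree with the protocol's own rule only at age 30 (29 or 31 at most under other rounding). Taken literally, the cutoff is 9, 18 and 27 bpm too high at 40, 50 and 60, and the lower work limit is too low for patients under 29.

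This rests on the document's 220-minus-age formula and on the absence of any example label. Whether any patient was affected depends on how the monitors were set and on the age mix, and the document gives neither. The design, sample size, alpha and power are not touched. The point should be fixed because it concerns a safety threshold and the defining dose of an intervention offered for replication. The session-length inconsistency is real but minor.

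**What to change.** 1. In Physical Exercise/Intervention Protocol, state that the warm-up zone, work zone and 90% cutoff are all percentages of the individual's 220 minus age, and that the Polar zones are set for each patient from age.
2. Delete the bpm values there and in the Abstract, or label them in both places as an example for age 30 (maximum 190 bpm).
3. For sessions already delivered, check that the monitors were set per patient, and report delivered intensity as a percentage of each patient's own maximum.
4. Minor: correct the session length, or say that the 30 minutes excludes the 5-minute cooldown and give the warm-up length.

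The cost is wording in two places and a check of the monitor settings. The design, sample size and analysis do not change.

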### Neuropsychological Testing

The present study is an intervention study as a follow up study from the Stayer longitudinal cohort study, and we will be using the some of the cognitive tests, that the Stayer study uses to follow the mental health of their participants. The test is listed below. All the neuropsychological testing will be performed by a research assistant who is specially trained to administer neuropsychological tests. The following paragraphs summarize the cognitive tests.

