1.Baseline testing. The physical and neuropsychological testing will be conducted within 2 weeks of admittance to the Salvation Army Treatment Center.2.The researchers will not conduct randomization, as there is natural allocation as a result of the SUD treatment allocation system, which will be continuous throughout the study.3.The control group is completed first. Structure is changed in the clinic and intervention group is started up after the last control patient has left the clinic.4.The intervention will consist of the physical exercise protocol, which will be conducted for 4 weeks.5.The final tests of physical function will be conducted the week after the exercise protocol is completed. The prospective follow-up will consist of cognitive testing carried out at 3, 6, 9, and 12 months after the baseline test.6.Discontinuation: Patients that don’t follow the protocol or don’t follow the TAU of the Facility will be discontinued. If they don’t complete the follow up test with in the allocated time line or neglect to perform the test they will be discontinued (Figure 1).

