#### Clinical Self-Rating Questionnaires

The Symptom Checklist-90-Revised (SCL-90-R) is a 90-item self-report symptom inventory developed by Derogatis (Derogatis and Unger, 2010) in the mid-1970s to measure psychological symptoms and psychological distress. It is designed for use with individuals from the community, as well as with individuals with either medical or psychiatric conditions. The SCL-90-R assesses psychological distress along nine primary symptom dimensions and three summary scores, which are referred to as global scores. The principal symptom dimensions are labeled Somatization (SOM), Obsessive-Compulsive (OBS), Interpersonal Sensitivity (INT), Depression (DEP), Anxiety (ANX), Hostility (HOS), Phobic Anxiety (PHOB), Paranoid Ideation (PAR), and Psychoticism (PSY). The three global measures are the Global Severity Index (GSI), the Positive Symptom Distress Index (PSDI), and the Positive Symptom Total (PST) (Derogatis and Unger, 2010).

The Satisfaction with Life Scale (SWLS) assesses subjective well-being by focusing on global life satisfaction. It does not tap related constructs such as positive affect or loneliness. The SWLS has favorable psychometric properties, including high internal consistency and high temporal reliability. Scores on the SWLS correlate moderately to highly with other measures of subjective well-being and correlate predictably with specific personality characteristics (Diener et al., 1985; Pavot et al., 1991).

The Behavior Rating Inventory of Executive Function–Adult Version (BRIEF-A) is a self-report form designed to be completed by adults 18–90 years of age, including adults with a wide variety of developmental, systemic, neurological, and psychiatric disorders, such as attention disorders, learning disabilities, autism spectrum disorders, traumatic brain injury, multiple sclerosis, depression, mild cognitive impairment, dementia, and schizophrenia. The BRIEF-A is composed of 75 items in nine non-overlapping and theoretically and empirically derived clinical scales that measure various aspects of executive functioning (Gioia et al., 2000; Kessler et al., 2005).

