#### Neuropsychological Tests

The Montreal Cognitive Assessment (MoCA) (Voluse et al., 2012) takes approximately 10 min to administer and is designed to detect mild cognitive impairment in elderly participants who score in the normal range on the Mini-Mental Status Examination. The MoCA uses 30 items to assess multiple cognitive domains, including: short-term memory (5 points); visuospatial abilities via clock drawing (3 points), and a cube copying task (1 point); executive functioning via an adaptation of the Trail Making Test Part B (1 point), phonemic fluency (1 point), and verbal abstraction (2 points); attention, concentration, and working memory via target detection (1 point), serial subtraction (3 points), digits forward (1 point), and digits backward (1 point); language via confrontation naming with low-familiarity animals (3 points) and repetition of complex sentences (2 points); and orientation to time and place (6 points) (Voluse et al., 2012). The MoCA is scored by obtaining an item total, and the authors recommend a clinical cutoff score of 26 (Voluse et al., 2012).

The Stroop Color and Word Test (SCWT) is used extensively to assess the ability to control the cognitive interference that occurs when the processing of a specific stimulus feature impedes the simultaneous processing of a second stimulus attribute, which is well known as the Stroop effect. The Stroop test has been used in previous trials on physical exercise and cognition and is a sensitive measure of prefrontally mediated cognitive functions (Bohn et al., 1995; Nasreddine et al., 2005).

The Trail Making Test is a test of visual attention and task switching. It consists of two parts in which the subject must connect a set of 25 dots as quickly and accurately as possible (Golden and Freshwater, 1978). The test provides information about visual search speed, scanning, speed of processing, and mental flexibility, as well as executive functioning (Arnett and Labovitz, 1995; Arbuthnott and Frank, 2000; Martínez et al., 2016; Scarpina and Tagini, 2017).

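### Enrolment date reveals the arm to the cognitive tester, so examiner-judged MoCA items are open to expectation bias; score them from stored forms with cohort, date and visit removed

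*Protocol article*

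**What the plan says.** Stepwise Procedures, item 3, fixes the order of the arms: "The control group is completed first", and the "intervention group is started up after the last control patient has left the clinic".

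Item 1 sets the baseline: "The physical and neuropsychological testing will be conducted within 2 weeks of admittance to the Salvation Army Treatment Center". Item 5 sets the follow-up: "cognitive testing carried out at 3, 6, 9, and 12 months after the baseline test".

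Neuropsychological Testing says who tests: "All the neuropsychological testing will be performed by a research assistant who is specially trained to administer neuropsychological tests".

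The Abstract states the expected direction. Both groups should improve, "with the exercise intervention group having the greatest increase in recovery of cognitive function".

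Neuropsychological Tests describes the MoCA as a 30-item scale. Its drawing items are worth 3 points (clock) and 1 point (cube). The Equipment section lists a computer for cognitive testing but does not say which tests run on it.

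No masking of tester, scorer or patient is described. The only mention of blind ratings concerns the validation sample of the ADHD self-report scale. Limitations of the Study accepts that running the groups in different periods may cause bias. It does not mention that the tester can know the arm.

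**The concern.** In a concurrent trial, a tester can be kept masked simply by not being told the allocation. Here that cannot work, because allocation is a function of when the patient entered. Whoever tests a patient can place that patient in the control or the intervention period without being told anything, and the team has put its expectation in writing.

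If expectation moves a judged score at follow-up in one cohort and not in the other, the group contrast shifts with no change in cognition. Separately, if the way items are scored changes as the study goes on, the change falls between the cohorts and cannot be told apart from the exercise effect. The acknowledged limitation covers differences between calendar periods in general, but not the tester's knowledge of arm, which is a separate mechanism and one that can be partly removed.

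**Working it through.** The plan gives no figure on this point, so there is none to reproduce. The check has three parts.

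**1. Can the arm be deduced at each visit?**

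Take the changeover in the clinic as month 0. Controls enrol before it and intervention patients after it.

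- Baseline: testing falls within 2 weeks of admission, so the test date alone places the patient before or after month 0.
- Follow-up: controls are followed for up to 12 months from baseline, so late controls can be tested in the same weeks as intervention patients, and the date alone no longer decides. Enrolment month is approximately test month minus visit month. Six months after the changeover, a 12-month visit gives 6 − 12 = −6 (control) and a 3-month visit gives 6 − 3 = +3 (intervention).
- Late visits: patients who miss a slot are tested as soon as possible, so this subtraction is approximate near the changeover. The enrolment date itself still settles the arm.

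The arm is therefore deducible at all five planned cognitive time points, for 60 patients × 5 = 300 planned assessments. This counts assessments where the arm can be known, not assessments that are biased.

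**2. Which bias survives the planned comparison?**

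Anticipated Results compares pretest with posttests and compares groups. Let the scoring shift be b0 at baseline and b1 at follow-up in the intervention cohort, and c0 and c1 in the control cohort. Then

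bias in the difference in change = (b1 − b0) − (c1 − c0).

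- If each cohort's shift is constant (b1 = b0 and c1 = c0), the bias is 0.
- If expectation acts at follow-up in the intervention cohort only, the bias is b1, in the predicted direction.
- If scoring practice drifts with calendar time, the bias depends on how the drift falls across the visits and can have either sign.
- In a group comparison of follow-up scores alone, the bias is b1 − c1, and a constant shift does not cancel.

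**3. How large could it be?**

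The drawing items carry 3 + 1 = 4 of 30 MoCA points. The document gives neither a MoCA SD nor a size for any shift. Assuming a between-patient SD of 2 to 3 points, an average follow-up shift converts as follows:

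| Assumed average shift (points) | Divided by SD 3 | Divided by SD 2 |
|---|---|---|
| 0.25 | 0.08 | 0.13 |
| 0.5 | 0.17 | 0.25 |
| 1 | 0.33 | 0.50 |

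A 1-point average would need a quarter of the drawing points to move, so it is a high value. The article's own threshold for clinical relevance is an effect size of 0.5.

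Sensitivity of the test: two-sample t-test, 30 per group, 58 degrees of freedom, two-sided 0.05, no true effect, bias b in SDs of the analysed score, noncentrality b × √(30/2) = 3.873 b.

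| Assumed bias (SD) | Rejection rate |
|---|---|
| 0 | 5.0% |
| 0.1 | 6.7% |
| 0.2 | 11.9% |
| 0.3 | 20.8% |
| 0.5 | 47.8% |

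These rows show how sensitive the comparison is. They do not estimate the bias in this trial.

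**The case against.** The strongest reply is that masking procedure is the kind of detail an article leaves to the full protocol. The text also does not say that the assistant scores the tests, delivers the training, or is one person throughout. This stands as far as it goes, so silence on masking is not itself the finding. But the sequential order is fixed in the article, and under it withholding allocation would not mask anyone. Only an active step, such as scoring records with the dates removed, would do so.

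Several stronger readings are tempting and are not supported.

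- **Test date alone gives the arm throughout.** This is true at baseline and during the stay only. At follow-up the visit month is needed as well.
- **Drift favours exercise.** Drift has no predictable sign and falls partly under the period bias that the authors already accept. Only expectation has a direction.
- **Any shift biases the result.** A shift that is constant within a cohort cancels in change from baseline.
- **The whole battery is hand-scored.** The article does not say so, and it lists a test computer. Examiner judgement is a fair inference for the MoCA drawings, and much less so for the Stroop and Trail Making tests.
- **The sequential order biases the self-ratings.** Patients know whether they do the circuit sessions under any design, so the exposure of scales such as the SWLS does not come from the order of the cohorts.
- **The plan gives self-ratings and performance tests equal weight.** No weights are stated, and the two groups of instruments have separate headings. Silence on ranking is not a statement of equality.

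**Conclusion.** The point holds in a limited form. Because the cohorts do not overlap in the clinic, enrolment date reveals the arm to the research assistant who does the cognitive testing, and the expected direction is on record. Examiner-judged items, chiefly the 4 MoCA drawing points, are open to expectation bias that can differ between baseline and follow-up. Changes in scoring practice over time are confounded with arm, in either direction. The stated limitation covers only the difference in time periods.

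The size is not derivable from the document. The conversions above rest on an assumed SD and assumed shifts, and show only that a modest bias would matter with 30 per group. The conclusion also assumes that the MoCA drawings are judged by a person, which the article implies but does not state. This supports a cheap safeguard. It does not show that the cognitive results will be biased, and it gives no reason to re-rank the outcomes: quality of life is a stated aim, and the timed tests would remain unmasked in any case.

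**What to change.** Keep the sequential design, the visits, the tests and the existing staff, and add the following.

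1. Store the paper MoCA forms. After follow-up ends in both cohorts, remove cohort, date and visit number, and score the judged items from both cohorts in one batch in mixed order, preferably by someone other than the person who administered them, who might recognise a form.
2. For any test run on the listed computer, take the recorded score directly.
3. Say in the limitations that the enrolment period reveals the arm to the tester, and that live and timed administration and the self-ratings remain unmasked.

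The cost is the work of masking forms and a delay before scores are available. No extra visit or assessor is needed, and no sample-size figure changes. Scoring all forms in one mixed batch also stops a change in scoring practice over time from lining up with arm for those items. The gain is partial, because only items that can be scored from a stored record are covered, and how a test was administered in the room cannot be masked afterwards.
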